In on-pump cardiac surgery procedures, lungs are not only prone to VILI and periprocedural atelectasis formation. Also, lung ischemia of the alveoli during the cardiopulmonary bypass (CPB) and the consequent lung ischemia/reperfusion injury (LIRI) after CPB termination as well as the extracorporeal circulation itself can cause lung injury which is mediated by hyperinflammation and can manifest at least in temporary organ dysfunction [8].

Every year over one million patients undergo on-pump cardiac surgery procedures worldwide. Due to frequent severe preoperative (pulmonary) comorbidities, invasiveness of the procedures, and the perioperative hyperinflammatory state, cardiac surgery patients are prone to lung injury. Thus, despite fast-track weaning protocols, approximately half of this patient population suffers from some kind of postoperative pulmonary complications (PPCs), ranging from hypoxemia (50%) and pneumonias (below 5%) to the acute respiratory distress syndrome (approximately 1%) [9]. Such postoperative complications extend intensive care unit stays, increase in-hospital mortality, and lead to adverse financial outcomes in health care [10].

As a result, the optimal ventilatory protocol for patients undergoing on-pump cardiac surgery is still under controversial debate. A very recent multicenter RCT (PROVECS trial) could not demonstrate the superiority of a general open-lung concept in various patient-relevant outcomes [9]. Also in non-cardiac surgery, more general and individualized (perioperative) open-lung approaches in large multicenter RCTs (PROVHILO and iPROVE trial) [11, 12] were not convincing in terms of PPCs prevention, even in obese patients (PROBESE trial) [13].

The aim of this trial is to investigate the potential role of individualized FCV as an alternative perioperative ventilation mode in on-pump cardiac surgery procedures and to compare this approach with “best clinical practice” PCV in terms of perioperative inflammation due to VILI, LIRI and invasiveness of the procedure as well as various peri- and postoperative patient-relevant outcomes.

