#### Important secondary outcomes of the main study

Oxygenation indices at different perioperative time points (Table 1, “art BGA”)Plasma IL-8 concentrations at different perioperative time points (Table 1)Perioperative ventilation pressures (mean and peak airway pressure, driving pressure), C_dyn_, airway resistances, and mechanical power of ventilation [26] up to 24 h after termination of CPBWeaning times from mechanical ventilationIncidence of postoperative pneumonias with the need of antibiotic treatment during the complete inpatient stay (suspected and/or confirmed, see below)Incidence of postoperative pulmonary complications (PPCs) during the first seven postoperative days including compound outcome analysis and single PPC analysis. PPCs encompass (modified from [20])New invasive ventilationNon-invasive ventilationPost-extubation respiratory acidosis (pH ≤ 7.3 and PaCO2 > 45 mmHg)ReintubationReadmission to ICU due to pulmonary reasonsMild hypoxemia defined as an PaO2/FiO2 < 300 but ≥ 200Moderate hypoxemia defined as an PaO2/FiO2 < 200 but ≥ 100Severe hypoxemia defined as an PaO2/FiO2 < 100Acute respiratory distress syndrome (ARDS) according to the Berlin criteria [27]Implantation of a veno-venous ECMOSuspected pneumonia defined as new pulmonary infiltrates plus 2 or more of the following clinical parameters: temperature > 38.5 or < 35.5°C, leucocyte count > 12 or < 4/nl and purulent secretions including antibiotic treatmentConfirmed pneumonia defined as pulmonary infiltrates and microbiological germ proof of tracheal aspirationsBronchoscopyPleural drainage due to pleural effusionsPleural drainage due to pneumothoraxIncidence of postoperative extra-pulmonary complications (PEPCs) during the first seven postoperative days including compound outcome and single PEPCs analysis. As PEPCs the following items are definedSepsis and septic shock (as defined in [28])Postoperative coronary interventionPostoperative wound infection with the need for antibiotic treatmentOther sites of infection with the need for antibiotic treatmentPericardial tamponade or other bleeding with intervention such as re-sternotomyImplantation of any device for extracorporeal life support (ECMO, Impella) or intra-aortic balloon pumpNon-pulmonary ICU readmissionAcute kidney injury with a Kidney Disease: Improving Global Outcomes (KDIGO) stage 2 or 3 [29]Postoperative delirium diagnosed by the Confusion Assessment Method for the ICU (CAM-ICU) [30]Systemic inflammatory response syndrome (SIRS) (according to [28]) free days during the first seven postoperative daysLengths of intensive/intermediate care unit stays and time to dischargeHospital readmission and mortality rate after one and 6 months post-surgery (Table 1, phone surveys)

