### Sample size {14}

The sample size was calculated according to the study hypothesis. Based on the previous results of protective ventilation protocols in the setting of on-pump cardiac surgery [21, 22], the effect size of the intervention on postoperative plasmatic IL-8 concentrations was estimated as moderate being well aware about the exploratory nature of this study of mid-term clinical FCV utilization. Under these assumptions (Cohen’s d = 0.5), the total sample size required to achieve a power of 1-β = 0.8 for a two-sample *t*-test at a two-sided level α = 0.05 resulted in 2*64 = 128 [36]. As the primary endpoint is obtained 6 h after termination of CPB, most dropouts will be due to a second cardiopulmonary bypass phase within this time frame or other in {11d} defined stop criteria in estimated 10% or less of the cases. Therefore, an additional 10% of patients will be randomized summing up to a total sample size of 128*1.1 = 140.8 ≈ 140 randomized study participants.

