## Statistical methods

### Statistical methods for primary and secondary outcomes {20a}

The intervention group (perioperative individualized FCV) will be compared with best clinical practice PCV as the control group for all primary analyses. The primary study endpoint will be assessed with a linear regression model using the intervention group as an independent variable and the EuroSCORE II as an additional covariable. For all continuous secondary endpoints, similar linear regression models will be fitted. All binary secondary outcomes will be calculated using a logistic regression model as well as SIRS-free days using a Poisson regression model with the same independent variables. For the analyses of multiple secondary outcomes, the Bonferroni method for appropriate adjustment of the overall significance will be utilized.

For all confirmative statistical analyses, 2-sided *p*-values with a significance level of 0.05 will be utilized. *P*-values will be reported to four decimal places with *p*-values less than 0.001 reported as *p* < 0.001. All analyses will be conducted with the statistical software R (www.r-project.org, version ≥ 4.1.0).

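### Ordinary logistic regression and Bonferroni applied to every binary secondary outcome suit neither the rarest single complications nor the separate hypoxaemia bands, and cost the composites power that could be kept

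*Protocol article*

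**What the plan says.** Section {20a} of the protocol article fixes one model for binary outcomes: "All binary secondary outcomes will be calculated using a logistic regression model", using the independent variables of the primary model (group and EuroSCORE II). For several secondary outcomes it adds that "the Bonferroni method for appropriate adjustment of the overall significance will be utilized". Confirmatory analyses use "2-sided *p*-values with a significance level of 0.05 will be utilized".

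The list of important secondary outcomes in {12} asks for PPCs "including compound outcome analysis and single PPC analysis", and likewise for PEPCs. Counting the list gives 15 single PPCs and 9 single PEPCs. Section {22}, on harms, refers these compound and single-item analyses back to {12} and {20a}. Neither the composites nor any item is given priority, and no single item is called descriptive.

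Three of the PPC items are hypoxaemia bands by PaO2/FiO2: 200 to below 300, 100 to below 200, and below 100.

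The background section {6a} supplies the only event rates: any PPC in about half of patients, hypoxaemia 50%, then "pneumonias (below 5%) to the acute respiratory distress syndrome (approximately 1" per cent).

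**The concern.** Three features of the stated rule cause difficulty.

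- **Sparse items.** The list includes events expected in one or two patients in the whole trial. If an arm has no event, ordinary logistic regression has no finite group odds ratio and a Wald test tells the reader nothing. These items are also the trial's record of possible harm in {22}.
- **Hypoxaemia bands.** Each band is closed at both ends except the lowest. A patient who worsens from mild to moderate leaves the mild band. If each patient is counted once by worst value, deterioration lowers the mild item.
- **Multiplicity.** Bonferroni gives every item the same small share of alpha. The composites, which belong to the key secondary objectives in {7}, then pay for two dozen component tests, some of which have no realistic chance of a result.

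**Working it through.** **Inputs.** Planned size from {14}: "at a two-sided level α = 0.05 resulted in 2*64 = 128", then "128*1.1 = 140.8 ≈ 140 randomized study participants", so 64 to 70 per arm at 1:1. Event rates from {6a}. The effect size in {14} concerns the primary endpoint only ("the effect size of the intervention on postoperative plasmatic IL-8 concentrations was estimated as moderate"). No effect is given for a binary outcome, so the effects below are assumptions.

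**The plan's own figure.** For a two-sample t-test with d = 0.5 and two-sided 0.05, the noncentral t distribution gives power 0.801 at 64 per arm and 0.795 at 63. The stated 64 per arm is right.

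**1. Empty arms.** With event rate p in both arms and n per arm, q = (1 − p)^n is the chance that one arm has no event, and 1 − (1 − q)² the chance that at least one arm has none.

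| p | 64 per arm | 70 per arm |
|---|---|---|
| 1% (ARDS) | q = 0.526; 77.5% | q = 0.495; 74.5% |
| 2% | 47.4% | 42.7% |
| 3% | 26.4% | 22.3% |
| 5% (ceiling for pneumonia) | 7.4% | 5.4% |

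At 1%, 128 to 140 patients yield 1.3 to 1.4 expected events. Neither arm has one in q² = 28% to 24% of trials.

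To show what the model then reports, take 0/64 against 6/64, unadjusted. The fitted odds ratio is about 5 × 10⁹ with Wald p = 0.999. Fisher's exact test gives p = 0.028 and a likelihood-ratio test p = 0.003.

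**2. Hypoxaemia bands.** Assumed worst-value distributions (mild/moderate/severe): PCV 35/10/5%, FCV 20/25/5%. Any hypoxaemia is 50% in both arms and FCV is worse within it.

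- Mild item: (0.20/0.80)/(0.35/0.65) = 0.46, favouring FCV.
- Moderate item: (0.25/0.75)/(0.10/0.90) = 3.0, against FCV.
- Cumulative cut-offs on the same data: below 300, 50% v 50%, OR 1.0; below 200, 30% v 15%, OR (0.30/0.70)/(0.15/0.85) = 2.4; below 100, OR 1.0. No cut-off points the wrong way.

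**3. Bonferroni and the PPC composite.** Control rate 50% ({6a}), assumed FCV rate 30%, 64 per arm. With a pooled variance under the null, power = Φ[(0.20 − z × √(2 × 0.4 × 0.6/64)) / √((0.25 + 0.21)/64)] = Φ[(0.20 − 0.0866z)/0.0848].

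- Unadjusted, z = 1.960: Φ(0.357) = 64%.
- 26 tests (15 + 9 + 2), alpha 0.00192, z = 3.102: Φ(−0.81) = 21%.
- Two composites only, alpha 0.025, z = 2.241: 53%.
- Seven tests, if each key secondary objective in {7} is one test (oxygenation, decarboxylation, PPCs, PEPCs, weaning, unit stay, time to discharge), alpha 0.00714, z = 2.690: 35%.

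At 70 per arm these are 68%, 24%, 57% and 39%. With 26 tests and 64 per arm, power is 2% for 50% to 40%, 8% to 35%, 43% to 25% and 69% to 20%. No PEPC composite rate is given, so its power cannot be computed.

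**The case against.** The best reply is that much of this is ordinary SAP content or is softened elsewhere in the article.

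- **The SAP is not shown.** Listing the family and naming a sparse-event fallback are usual SAP content, and their absence is not counted here. {20a} names neither maximum likelihood nor a Wald test, and Firth regression is itself a logistic model. That stands as a limit: the problem applies to ordinary logistic regression, which is how the sentence would normally be read.
- **The test matters.** A likelihood-ratio test handles the 0/64 v 6/64 table. It does not supply a finite odds ratio, so the estimation problem remains. The table is an illustration and would be very unlikely at a true 1% in both arms.
- **Hypoxaemia is reported from several sides.** The moderate and severe items, the PPC composite and the oxygenation indices stand beside the mild item, so an overall false verdict of benefit is unlikely. The reversal also needs worst-value counting, which {12} does not state, and assumed rates. What stands is that one listed item can point the wrong way.
- **The trial was sized for IL-8** and {14} calls it exploratory. The composite is underpowered even at 0.05, so Bonferroni is not the only cause, and Bonferroni does control the error rate.

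A reader might infer that the single items as a group cannot be estimated, or that the clinical secondary outcomes cannot reach significance. Neither follows. At 5% the model can usually be fitted, and even with 36 tests at 64 per arm the composite has 39% power for a fall to 25% and 65% for a fall to 20%. Nor should mechanical power be set aside as a mere ventilator setting. {12} lists it as a secondary outcome and {6a} says clinical data on its reduction are lacking.

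**Conclusion.** The point holds in a limited form and should be corrected. For items near 1%, the stated model fails to give a finite group odds ratio in roughly three trials in four (74–78%). This rests on the article's ARDS rate applied to both arms. At 5% it is a minor matter (5–7%).

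The mutually exclusive hypoxaemia bands can show apparent benefit on the mild item when patients worsen, provided that worst-value counting is used. The size shown (OR 0.46) depends on assumed rates.

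Bonferroni is valid but needlessly conservative. Read plainly over 26 tests, it takes composite PPC power from 64% to 21% at 64 per arm for an assumed fall from 50% to 30%. The family of 26 is a reading of {12}, {20a} and {22}, not a stated number. None of this touches the primary IL-8 analysis.

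**What to change.** Amend {20a}, and the PPC list in {12} where needed:

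1. Report sparse single PPCs and PEPCs as counts per arm with risk differences and exact or score confidence intervals. Where an adjusted odds ratio is wanted, use Firth-penalised logistic regression.
2. Analyse hypoxaemia by cumulative cut-offs (PaO2/FiO2 below 300, below 200, below 100) or as one ordinal outcome, the worst category over the seven days. State the counting rule.
3. Limit the tested family to the key secondary objectives in {7}, with PPCs and PEPCs entering as composites, and treat single components as descriptive. Replace Bonferroni by Holm, which controls the same error rate and is never less powerful. Most of the gain comes from the shorter family (21% to 35% at seven tests in the example, before any further gain from Holm).

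Mechanical power stays a secondary outcome. The cost is analysis wording only, with no change to data collection or sample size. The downside is that fewer items carry a formal significance claim, and the composite would still be underpowered for moderate effects.

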### Intervention description {11a}

#### General setting

General anesthesia is induced with sufentanil (bolus of 0.3–0.5 μg/kg), propofol (initial bolus of 0.5–1.5 mg/kg following titration depending on the Bispectral index), and pancuronium (bolus of 0.05–0.1 mg/kg) i.v. according to departmental standards. As no volatile anesthetics can be administered technically by the FCV ventilator, total intravenous anesthesia is maintained in both groups by continuous sufentanil (0.5–0.6 μg/kg/h) and propofol infusion (4–6 mg/kg/h) for an intraoperative Bispectral index of 40–50 during the pre- and intraoperative period. During CPB, propofol infusion is suspended and sevoflurane is administered systemically through the membrane oxygenator of the extracorporeal circulation.

After intubation with a conventional tube (ID 8–8.5 mm) and verification of correct tube position by capnometry and auscultation in both groups, patients in the FCV group are additionally equipped with a conventional tube adapter (Ventinova Medical, Eindhoven, the Netherlands). Group-specific invasive ventilation is initiated in a supine position at a PEEP of 5 cm H_2_O and a DP for a V_t_ of 6–8 ml/kg PBW in both groups. PBW is calculated according to PBW = 45.5 + 0.91*(height in cm − 152.4) for female and PBW = 50 + 0.91*(height in cm − 152.4) for male participants.

The respiratory rate in the PCV and airway flows in the FCV group are set to maintain sufficient decarboxylation (arterial pCO_2_ 35–45 mmHg) throughout perioperative mandatory ventilation. Fraction of inspired oxygen (FiO_2_) of the respective respirator is kept in both groups at 0.8 by default throughout the pre- and intraoperative phase.

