**Table 1 Tab1:**
[figure not shown]
Time schedule for enrolment, allocation, interventions and assessments in the main and ancillary studies. Calculations for the Assess Respiratory Risk in Surgical Patients in Catalonia (ARISCAT) Score [34] can only be completed when SpO_2_ is measured at the time of patient arrival in the induction room. The EuroSCORE II [35] is recalculated after CPB based on the actual intraoperative cardiac surgical interventions. Additional arterial BGAs are conducted simultaneously to the EIT recordings on CPAP and pressure support ventilation during weaning as well as 30–60 min after extubation. Close-out of participants is after the second phone survey 6 months after the cardiac surgery procedure. The first phone survey is conducted one month postoperatively. Post-allocation time points: Base, patient breathing spontaneously before induction of anesthesia; T−2, after group-specific individualization of ventilation and before skin incision; T−1, 15 min after thoracotomy; T0, after CPB termination and transfusion stop from the extracorporeal circulation; T1–24, appropriate hour after CPB end. BGA, blood gas analysis; BNP, brain natriuretic peptide; CK-MB, creatine kinase MB; CPAP, continuous positive airway pressure ventilation during weaning; PEEP, positive end-expiratory pressure; PEPCs, postoperative extra-pulmonary complications; POD, postoperative day; PPCs, postoperative pulmonary complications

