## Discussion

During on-pump cardiac surgery procedures, lungs do not only need to withstand mid-term invasive ventilation in deep general anesthesia, surgical manipulations, and recurrent phases of apnea with consecutive atelectasis formation and atelectrauma. Lungs also receive a further hit by partial ischemia and reperfusion through the use of CPB, resulting in LIRI. These various injuries and their combination induce a pulmonary and systemic hyperinflammatory state [8, 37] which to a large extent accounts for the common postoperative pulmonary dysfunctions [10]. Clinical studies in the setting of cardiac surgery could demonstrate a reduction of key inflammatory biomarkers when lung protective ventilation strategies with respect to an open-lung approach [22] and combined with low tidal volumes [21] were applied perioperatively. However, the recent multicenter study PROVECS could not show a clinical benefit towards PPCs prevention when comparing a perioperative, generalized open-lung concept with common practice ventilation in cardiac anesthesia [9].

The trial scope of FLOWVENTIN HEARTSURG is to evaluate the new ventilatory mode of FCV in a single center RCT of a medium sample size in a perioperative approach. We did not exclude any preexisting patient comorbidities per se, except for situations with an initially modified (hyper-) inflammatory environment like in acute myocardial infarction and preexisting pneumonia as well as (suspicion of) endocarditis or intake of any preoperative immunosuppressive medication. The same open approach was chosen for the surgery: All types of single and combined surgical procedures with the exception of heart transplantation and assist device implantations are allowed as on-pump interventions. The reasoning behind this was to have a really thorough sample of cardiac surgical patients and procedures as the basis for our study. However, statistical analysis will adequately account for preoperative comorbidities and the severity of surgery as the EuroSCORE II will function as an additional covariable that specifically weighs patient-, cardiac-, and operation-related factors in the analysis of primary and secondary endpoints.

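### Secondary outcomes are adjusted only for EuroSCORE II; adding ARISCAT and predicted body weight, both already available, is an optional, cheap gain in efficiency

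*Protocol article*

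**What the plan says.** Section {20a} fits the primary endpoint by linear regression on arm and EuroSCORE II. Continuous secondary endpoints get linear models of a similar kind. For the rest, "All binary secondary outcomes will be calculated using a logistic regression model", and SIRS-free days are analysed by Poisson regression; both use the same independent variables as the primary model. The Discussion confirms the choice for primary and secondary endpoints and gives the reason: "the EuroSCORE II will function as an additional covariable that specifically weighs patient-, cardiac-, and operation-related factors".

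Two other values exist for every patient before allocated ventilation begins:

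- **ARISCAT.** The Table 1 legend says that its calculation "can only be completed when SpO_2_ is measured at the time of patient arrival in the induction room". That is before induction, and so before any allocated ventilation.
- **PBW.** Under General setting in {11a}, "PBW is calculated according to PBW" introduces a formula in height and sex, applied in both arms.

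The article names neither as a covariate. The secondary outcomes in {12} include oxygenation indices, dynamic compliance (C_dyn), airway resistance, mechanical power, pneumonia and the PPC composite. Section {16a} describes permuted blocks and names no stratification factor.

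**The concern.** EuroSCORE II is described as weighing patient, cardiac and operative factors. Most of the secondary outcomes above are respiratory, and some are likely to depend on lung size. The Discussion says that no comorbidity is excluded as such beyond those that alter the inflammatory state, and the Background describes frequent severe pulmonary comorbidity. Respiratory risk and body size may therefore vary widely between patients. With about 64 evaluable patients per arm and no stratification, they may also differ between arms by chance.

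Efficiency is at stake. A prognostic baseline covariate removes residual variance in a linear model and raises the power of the arm test in a logistic model. Both candidate covariates are already in hand. Naming them in advance also avoids choosing covariates after an imbalance has been seen. The primary IL-8 analysis is not affected.

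**Working it through.** **1. The plan's own figure.** Section {14} uses a standardised difference of 0.5, "two-sided level α = 0.05" and "power of 1-β = 0.8", which "resulted in 2*64 = 128". The normal approximation gives n = 2(1.96 + 0.8416)²/0.5² = 62.8, so 63 per arm. The exact noncentral-t calculation gives 63.77, so 64 per arm, with power 0.801. The plan's figure reproduces. Then "an additional 10% of patients will be randomized": 128 × 1.1 = 140.8, taken as 140. This concerns IL-8 only; the article states no power for any secondary outcome.

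**2. Inputs that the article does not give.** It gives no prognostic strength for ARISCAT or PBW and no PPC rate under FCV. These are assumed below. A control PPC rate of 50% follows the Background section.

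**3. Continuous outcomes.** If a covariate explains a further share R² of the residual variance, the SE is multiplied by √(1 − R²). The noncentrality at N = 128 is (0.5/√(1 − R²)) × √(128/4).

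| Added R² (assumed) | SE ratio | Noncentrality | Power at d = 0.5 |
|---|---|---|---|
| 0 | 1.000 | 2.83 | 0.801 |
| 0.05 | 0.975 | 2.90 | 0.821 |
| 0.10 | 0.949 | 2.98 | 0.841 |
| 0.20 | 0.894 | 3.16 | 0.881 |

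If two added covariates explain nothing, the SE rises by √(124/122) = 1.008, about 0.8%. For one added covariate it is √(124/123) = 1.004.

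**4. PPC composite.** This was simulated with 64 per arm, marginal risks of 50% v 27% (the second assumed), EuroSCORE II log-odds of 0.3 per SD (assumed), 4000 runs, a Wald test at 0.05, and ARISCAT as the only added covariate. Two separate sets of runs gave the power figures below. The last column is the median SE of the log odds ratio from a further run of the same scenario.

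| ARISCAT log-odds per SD (assumed) | Power, first set | Power, second set | Median SE of log-OR |
|---|---|---|---|
| 0 | 77.7% v 77.8% | 78.2% v 78.3% | not recorded |
| 0.5 | 77% to 79% | 77.9% to 79.6% | 0.386 to 0.402 |
| 0.8 | 77% to 83% | 77.4% to 81.5% | 0.385 to 0.420 |
| 1.1 | 76% to 85% | 76.6% to 84.6% | 0.384 to 0.442 |

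The SE rises while power rises. Conditioning on a prognostic covariate moves the log odds ratio further from zero, by more than the SE grows. Under the null at log-odds 0.8, rejection was 5.2% without ARISCAT and 4.8% with it.

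A less favourable set-up gives smaller gains. It used N = 140, a conditional odds ratio of 0.4, ARISCAT correlated 0.4 with EuroSCORE II, and both ARISCAT and PBW added, PBW having no effect. Power went from 0.735 to 0.731 at log-odds 0, 0.690 to 0.693 at 0.3, 0.685 to 0.704 at 0.6, and 0.585 to 0.642 at 1.0.

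**5. Pneumonia.** The Background puts it below 5%, so at most 0.05 × 140 = 7 events. Events per non-intercept parameter are 7/2 = 3.5 as planned, 7/3 = 2.3 with one more covariate and 7/4 = 1.75 with two. In simulation with an assumed odds ratio of 0.4, about a quarter of fits were not estimable with either model. At an ARISCAT log-odds of 0.6, adding both covariates widened the SD of the estimate from 0.824 to 0.973.

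**The case against.** The strongest case against is that nothing here is wrong. One covariate is prespecified, with a stated reason that suits a deliberately mixed surgical population. Randomisation makes the arm comparison valid without ARISCAT or PBW, and no stated figure is contradicted. All of that stands.

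The benefit is also assumed throughout. One assumption deserves particular caution: tidal volume is set per kg PBW in the control arm throughout, whereas the FCV arm is titrated by compliance. A single correlation between PBW and mechanical power across both arms is therefore doubtful. This is why the table uses a range of added R².

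The calculations use alpha 0.05, whereas {20a} applies Bonferroni to multiple secondary outcomes. With an assumed 10 tests and ARISCAT log-odds of 0.5, PPC power is about 43% without ARISCAT and 46% with it. The covariate is then not what chiefly limits that comparison.

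A reader might infer that the plan gives up free precision for PPCs, pneumonia and lung mechanics alike. The checks do not support that. In a logistic model the SE of the log odds ratio rises and only power improves; for pneumonia an extra covariate does harm. Nor can one conclude that ARISCAT is used in no analysis at all: the article condenses a fuller German protocol, and an analysis plan may exist. What can be said is that the article's stated models name only EuroSCORE II.

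**Conclusion.** The planned secondary analyses are valid and unbiased. They may be somewhat less efficient than the collected data allow.

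For the PPC composite, the likely gain is in power: about 2 points at an ARISCAT log-odds of 0.5 per SD and about 8 at 1.1. It is close to nil if ARISCAT is weak. For continuous outcomes the gain is in precision: power at d = 0.5 goes from 0.80 to 0.84 or 0.88 at an added R² of 0.10 or 0.20. These figures rest on assumed prognostic strength, an assumed PPC rate under FCV and an unadjusted 0.05 level. For pneumonia and other rare items there is no useful gain.

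A reader might take this as an error, or as bias from chance imbalance; the article supports neither. It is an optional, cheap improvement.

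**What to change.** Before unblinding, amend {20a} as follows:

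- For the PPC composite and the oxygenation indices, add ARISCAT to arm and EuroSCORE II, as a continuous score in the version completed on arrival in the induction room.
- For C_dyn, airway resistance and mechanical power, add PBW to arm and EuroSCORE II.
- For pneumonia and other rare single items, add no further covariate.

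The cost is one or two sentences and one degree of freedom per model, with no new data. The PPC odds ratio becomes conditional on ARISCAT as well as EuroSCORE II, with a larger SE on the log-odds scale, and the report should say so.

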### Trial design {8}

FLOWVENTIN HEARTSURG is designed as a randomized, controlled, single-center, superiority trial with two parallel groups. The group assignment will be performed by block randomization with an 1:1 allocation.

In different ancillary studies, the effect of FCV versus PCV on perioperative lung aeration based on EIT-derived data as well as right ventricular, echocardiographic function parameters will be investigated following an exploratory approach.

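### Holm's step-down method could replace Bonferroni for the secondary outcomes at the same familywise error; the gain in power is real but usually small

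*Protocol article*

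**What the plan says.** Section {20a} of the protocol article fits regression models to the secondary endpoints and then fixes the multiplicity method: "For the analyses of multiple secondary outcomes, the Bonferroni method for appropriate adjustment of the overall significance will be utilized". The ordinary reading is the single-step procedure, in which each of m tests is compared with 0.05/m; no step-down version is named. Confirmatory analyses use two-sided p-values "with a significance level of 0.05 will be utilized", and p-values "less than 0.001 reported as" an inequality, without the exact value.

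Section {12} lists the secondary outcomes, including composite and component-by-component analyses of the pulmonary and extra-pulmonary complications and several measures at more than one time. The article states neither m nor a per-test level. Section {14} sizes the trial on the primary endpoint alone, where the calculation "resulted in 2*64 = 128". It makes no power claim for any secondary outcome.

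**The concern.** Single-step Bonferroni holds every test at 0.05/m however many of the others have been rejected. Holm's procedure relaxes the threshold after each rejection and keeps the same guarantee. Where one method never rejects less than another at the same error rate, the weaker one needs a reason, and the article gives none.

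The structure of this trial makes the question more than academic. The secondary list mixes clinical outcomes with ventilation measures that the two strategies set or target directly: mean and peak airway pressure, driving pressure, compliance, resistance and mechanical power. Large arm differences on some of these are plausible by design, although the article gives no size for them. Under Bonferroni, such rejections do nothing for the remaining tests. Under Holm, each one eases the threshold for complications, oxygenation and weaning, which belong to the key secondary objectives in section {7}.

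**Working it through.** **1. The plan's own figure.** A two-sample t-test with d = 0.5, power 0.80 and two-sided 0.05 needs 63.77, so 64 per arm and 128 in total (exact power 0.801). Then 128 × 1.1 = 140.8, stated as 140. The sample size reproduces. There is no stated figure for the Bonferroni step to reproduce.

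**2. Why Holm is never worse.** Order the p-values and compare the i-th smallest with 0.05/(m − i + 1), stopping at the first failure.
- *Rejections.* 0.05/(m − i + 1) is at least 0.05/m. Any p-value at or below 0.05/m is preceded only by smaller ones, and all of them pass. So every Bonferroni rejection is also a Holm rejection.
- *Error rate.* With m₀ true null hypotheses, the first false rejection must occur at a step whose threshold is at most 0.05/m₀. By the union bound its probability is at most m₀ × 0.05/m₀ = 0.05. No assumption about dependence is used.

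**3. A working value for m.** Counting each item of section {12} once:

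| Item | Tests |
|---|---|
| Oxygenation; IL-8 | 2 |
| Ventilation measures | 6 |
| Weaning time; pneumonia during the inpatient stay | 2 |
| Pulmonary complications: composite + 15 single | 16 |
| Extra-pulmonary complications: composite + 9 single | 10 |
| SIRS-free days | 1 |
| Lengths of stay | 2 |
| Readmission and mortality, two times each | 4 |
| **Total** | **43** |

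This count is an assumption about the family; the article does not fix it.

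**4. Power of one test.** By the normal approximation with 64 per arm and d = 0.5, the expected z is 0.5 × √(64/2) = 2.83.
- At 0.05: Φ(2.83 − 1.96) = 0.807.
- At 0.05/43 = 0.00116: Φ(2.83 − 3.25) = 0.337.
- At 0.05/37 = 0.00135, the level Holm reaches once six tests have been rejected: 0.353.

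**5. Full procedure by simulation.** Settings: 40,000 trials per scenario, m = 43, 64 per arm, moderate effects d = 0.5, large effects d = 1.5, the rest null, correlation 0 and 0.3 (similar results). Average power per moderate effect:

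| Real effects | Bonferroni | Holm | Gain (points) |
|---|---|---|---|
| 5 moderate, 0 large | 33.7% | 34.0% | 0.3 to 0.4 |
| 5 moderate, 6 large | 33.7% | 35.8% | about 2.1 |
| 10 moderate, 6 large | 33.7% | 36.3% | about 2.6 |
| 10 moderate, 10 large | 33.8% | 37.8% | about 4 |

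Familywise error stayed below 0.05 for both methods, and no simulated trial had a Bonferroni rejection that Holm missed.

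**6. The p-value format.** 0.05/43 = 0.00116, 0.05/50 = 0.00100 and 0.05/51 = 0.00098. At m = 43 a printed value below 0.001 does show that the criterion was met. Testing oxygenation, IL-8 and the six ventilation measures at two times each adds 8 tests: 43 + 8 = 51. From there the printed inequality no longer settles the matter, provided raw p-values are being compared with 0.05/m.

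**The case against.** The strongest reply is that nothing here is wrong. Bonferroni is prespecified, valid and conservative; it cannot inflate error or bias an estimate. That stands: this is an efficiency point, not an error or a contradiction.

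A reader might infer that true secondary effects are being lost for nothing. The documents do not support that, for three reasons:
- Most of the fall in power comes from controlling familywise error over many tests. At m = 43 the fall is from about 81% to 34%, and in the scenarios with up to six large effects Holm recovers at most about 2.6 of those points.
- The smallest p-value must meet 0.05/m under both methods, so the chance of at least one secondary rejection is identical.
- Bonferroni has simple simultaneous confidence intervals that match its tests, and Holm does not. The article plans no such intervals, so the loss is small, but it exists.

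Larger gains can be produced only by stronger assumptions. They reach about 12 points per effect when every outcome in a family of 5 or 10 is truly different, and 5 to 7 points with 67 or 100 tests of which 24 or 50 show very large effects. Nothing in the article supports those settings. Many of the 43 outcomes are also binary and some are rare (section {6a} puts ARDS at about 1% and pneumonia below 5%), so a normal test with d = 0.5 represents them poorly.

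It is also tempting to say that the p-value format hides which results passed. That follows only if m exceeds 50 and raw p-values are shown, and the article states neither. With Bonferroni-adjusted p-values the criterion stays at 0.05 and nothing is hidden. The size of the family may be set in a document not shown, so its absence is no finding.

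**Conclusion.** The point holds as a cheap, optional improvement. Holm gives the same familywise error control under any dependence and never rejects less, so the stated method gives up some power with nothing gained in error control. At 43 tests the gain per true moderate effect is about 0.4 points with five such effects and no large ones, and about 2 to 3 points if the six ventilation measures also differ strongly.

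That Holm is never worse needs no assumption. The sizes rest on m = 43, 64 evaluable patients per arm, d = 0.5 carried over from the primary endpoint, d = 1.5 for the large effects, and normal tests. The remark on p-value format is conditional and applies only with more than 50 tests and raw p-values.

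**What to change.** In section {20a}, name the Bonferroni-Holm step-down method in place of the Bonferroni method, and report Holm-adjusted p-values for the secondary outcomes beside the raw ones. Make the change before unblinded data are analysed. If more than 50 secondary tests are made and raw p-values are printed, give values below 0.001 exactly, for example to two significant digits.

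The cost is a few words in the plan and one option in R, which is already the specified software. No data, patients or assumptions are added. The one downside is that simple simultaneous intervals matching the tests are lost, so ordinary 95% confidence intervals would be shown and labelled as unadjusted.
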